### Tertiary endpoint

Finally, the tertiary endpoint aims to observe the changes of indicators (anthropometry, laboratory assessment, imaging examination) before and after bariatric surgery, and compare the correlation between QUS and traditional evaluation indices. It may indicate whether there are differences in these indicators before and 1, 3, 6 and 12 months after bariatric surgery, and these differences will assess the influence of bariatric surgery on these indicators.

## Stopping rules

(1)Patient's voluntary withdrawal;(2)The subject's request to withdraw their informed consent;(3)Medical necessity for discontinuation of the study by the researchers, etc.

### Sample size

To ensure accurate evaluation of QUS techniques for hepatic steatosis grading, it is imperative to calculate the required sample size. Assuming an 80% MAFLD prevalence in the target population and 80% sensitivity and 90% specificity in QUS techniques, we calculated the minimum number of subjects needed to be 75 using a paired non-parametric test in the non-parametric module of PASS. Considering factors like data loss, cases “lost to follow-up”, our study will involve 100 patients scheduled to undergo RYGB.

### Data management

For maintaining personal information confidentiality, enrolled patients will be assigned a unique identification number that will replace their real names throughout the clinical project. A trained researcher will document and submit data accuracy and completeness via CRFs to an expert committee for review. The collected data will be entered into a specialized database through an electronic CRF for secure storage. When all participants complete the study, the dataset will be analyzed accordingly.

### Data analysis

The statistical analysis for this study will be performed using the SAS 9.2 software package (SAS Analytics, Marlow, UK) and R (v4.3.1; R Core Team), which is widely available for commercial use. The significance level has been predetermined to be 0.05 for all two-sided tests. The mean and standard deviation will be used to express normally distributed quantitative data.

To compare quantitative data, a paired t-test will be employed. Meanwhile, categorical variables will be analyzed using the chi-squared test. Pearson correlation coefficients will be utilized to evaluate the relationship between QUS parameters and other factors under consideration. Univariable linear regressions of QUS and other methods on MRI-PDFF were conducted to calculate the adjusted linear correlation coefficient (r). Then receiver operating characteristic (ROC) curves of QUS and other methods for the detection of MRI-PDFF ≥5% and ≥10% were plotted. The best cut-off values were defined as the cut-off values corresponding to the maximum Youden indexes.

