### I (intervention)

All patients will receive anthropometric measurements (BMI, waist circumference, hip circumference), blood-based biochemical analyses (alanine aminotransferase ALT, aspertate aminotransferase AST, γ-glutamine transferase γ-GTP, total cholesterol Tc, triglyceride, high-density lipoprotein cholesterol HDL-c, low-density lipoprotein cholesterol LDL-c), ultrasonic examination (B-mode US, CAP, TAI, TSI) and magnetic resonance imaging proton density fat fraction (MRI-PDFF) before and 1, 3, 6, 12 months after bariatric surgery.

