### Secondary endpoint

The secondary endpoint focuses on evaluation of hepatic steatosis and its changes in obese individuals before and after bariatric surgery using QUS techniques (TAI, TSI) over a period of 1, 3, 6, and 12 months. Interpretation of the data collected will depend on whether significant differences are observed in QUS parameters pre- and post-surgery. The confirmation of such differences would furtherly signify the feasibility of using QUS techniques for postoperative evaluation of bariatric surgery. In addition, the trend in the changes of hepatic steatosis would evaluate the influence of bariatric surgery on obese individuals.

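### Separate paired t-tests on five-visit data use a different subset at each time point, and can misstate the size and trend of the change if patients are lost in relation to response

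*Protocol article*

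**What the plan says.** The intervention section schedules all anthropometric, laboratory, ultrasound and MRI-PDFF assessments "before and 1, 3, 6, 12 months after bariatric surgery", which makes five visits per patient.

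The Secondary endpoint section is about steatosis and its change on the QUS parameters over the four postoperative visits. It states that "Interpretation of the data collected will depend on whether significant differences are observed in QUS parameters pre- and post-surgery", and it also intends to read the trend in those changes as a measure of the effect of surgery. The Tertiary endpoint section asks "whether there are differences in these indicators before and 1, 3, 6 and 12 months after bariatric surgery" for the anthropometric, laboratory and imaging indicators.

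The Data analysis section sets the error rate ("The significance level has been predetermined to be 0.05 for all two-sided tests") and names one method for comparing quantitative data: "To compare quantitative data, a paired t-test will be employed". Correlation, linear regression on MRI-PDFF and ROC curves are named for the other questions.

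Losses are foreseen. The Sample size section moves from a minimum of 75 to the statement that "our study will involve 100 patients scheduled to undergo RYGB", citing data loss and loss to follow-up. The Stopping rules section lists routes of withdrawal. No loss rate, by visit or overall, is given.

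**The concern.** A paired t-test answers a two-visit question; the endpoints describe a five-visit course. Run separately for months 1, 3, 6 and 12, the tests have two consequences once patients leave.

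- The four mean changes come from four possibly different groups of patients, so a trend read across them mixes change within patients with change in who is still attending.
- The 12-month test makes no use of the month 1, 3 and 6 values of a patient who left before month 12, although those values are informative about the missing one.

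If patients who respond poorly are more likely to stop attending, the remaining patients show too large a fall in QUS and PDFF. If better responders leave, the error runs the other way. What is at stake is the estimated size and time course of the change in the secondary and tertiary endpoints.

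**Working it through.** **Inputs from the article.** Five visits (I (intervention)); paired t-test, two-sided 0.05 (Data analysis); minimum 75 and enrolment of 100 (Sample size).

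**Step 1: the plan's own figures.** 75 / (1 − 0.25) = 100, so the step from 75 to 100 equals an allowance of 25%. The 75 itself cannot be confirmed, because power and the tested hypothesis are not given. A McNemar approximation with discordant cells 0.8 × 0.2 = 0.16 and 0.2 × 0.1 = 0.02 gives 70, 80 and 93 (two-sided, power 80%, 85%, 90%), and 75 only if one-sided with 90% power. Nothing below depends on this: the 75 rests on prevalence, sensitivity and specificity, not on the change analysis. The 25% is used only as a working assumption.

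**Step 2: extent.** The continuous measures are 3 anthropometric, 7 laboratory, CAP, AC-TAI, SC-TSI and MRI-PDFF, that is 14. Over four postoperative visits this is 14 × 4 = 56 paired tests, of which 2 × 4 = 8 (AC-TAI and SC-TSI) serve the secondary endpoint.

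**Step 3: random loss.** With correlation ρ between baseline and month 12 and m patients seen at both, the standard error of the mean change in SD units is √(2(1 − ρ)/m). With m = 75:

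- ρ = 0.5: √(1.0/75) = 0.115
- ρ = 0.7: √(0.6/75) = 0.089

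Simulation gives the same values, no bias and 95% coverage of 0.95. A likelihood estimate using all visits has a smaller standard error. With serial correlation (0.5 or 0.7 raised to half the visit lag) it is 0.133 against 0.142, and 0.110 against 0.117, about 6% smaller. Across the settings tried the gain was about 2 to 8%.

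**Step 4: loss that depends on the response already observed** (assumed; n = 100, monotone loss after month 1, poorer responders leave more often). Bias of the paired 12-month change:

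| Assumptions | Bias, SD | 95% CI coverage |
|---|---|---|
| 10% loss, equal correlation 0.5–0.7, odds ratio of loss 1.5–3 per SD, true change −1.2 SD | −0.01 to −0.05 | 0.95 to 0.92 |
| 25% loss, otherwise the same | −0.03 to −0.13 | 0.93 to 0.80 |
| 25% loss, stronger dropout (log-odds slope up to 2 per SD), equal or serial correlation | −0.06 to −0.28 | down to 0.43 |

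Check of one cell: bias 0.128 and SE 0.115 give a ratio of 1.11, so coverage is about Φ(1.96 − 1.11) = Φ(0.85) = 0.80, as simulated. The top of the range needs a slope of 2, an odds ratio of e² = 7.4 per SD, together with serial correlation. Equal correlation with the same slopes gives 0.06 to 0.18 SD. In the settings where a likelihood estimate from all visits was also computed, its bias was 0.01 SD or less.

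**Step 5: loss that depends on the unseen 12-month value** (25% loss, correlation 0.5, odds ratio 2–3). Paired t-test bias is about −0.17 to −0.25 SD; the likelihood estimate has about −0.08 to −0.13 SD. The bias is roughly halved, not removed.

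**Step 6: effect on significance.** With an assumed fall of 1 SD and standard errors of 0.117 to 0.142, t is 1/0.142 = 7.0 to 1/0.117 = 8.5. A bias of 0.1 SD or a 6% change in the standard error does not alter that conclusion.

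**The case against.** Several points on the other side are sound.

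- Each paired t-test is a legitimate test of its own contrast, and the endpoints do ask for pre/post differences. A reader might infer that a patient with any missed visit is dropped altogether. That is not so: a patient missing only month 3 stays in the baseline-to-month-12 test, and each intermediate visit enters its own comparison.
- A reader might infer that the article forecasts a quarter of patients lost by month 12. It does not. The step from 75 to 100 is a reserve that covers data loss as well as loss to follow-up.
- A reader might infer that the 12-month result will be biased. No passage says who leaves or why; the listed withdrawal routes do not point to poor response. Under unrelated loss the bias is zero.
- A reader might extend the point to the primary endpoint, or ask for clustering in ROC curves pooled over visits. The primary comparison with MRI-PDFF uses correlation, regression and ROC, and the Data analysis section does not say that visits will be pooled.
- Rules for missing visits may sit in an analysis plan that is not shown, so their absence from an article is no fault.

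What remains is that the article itself fixes the comparison method, and that method does not match a five-visit course and trend when losses are expected. An unseen plan could add detail, but the stated method would still need replacing.

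**Conclusion.** The point stands in conditional form, for the secondary and tertiary endpoints. The named test leaves the four changes resting on possibly different patients and makes no use of the earlier visits of those who leave. If 25% are lost in relation to observed response, the 12-month change is misstated by roughly 0.03 to 0.28 SD. At 10% loss under the milder assumptions it is 0.01 to 0.05 SD. If loss is random there is no bias, and the cost is a standard error a few percent too large. Loss rate, mechanism, correlation and true change are all assumptions, and the direction shown applies when poor responders leave. A change to the analysis is worth making, but it improves estimation: a large fall would very probably be significant either way.

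**What to change.** In the Data analysis section, replace the separate paired t-tests by one linear mixed model for repeated measures for each continuous measure: all five visits as response, visit as a factor, unstructured covariance within patient, all observed data. Report the four changes from baseline with 95% CIs, and identify those for AC-TAI and SC-TSI as the secondary endpoint. Add a sensitivity analysis in which patients who leave are allowed to have a poorer course than the model predicts from their observed visits.

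The cost is analysis wording and standard code in the SAS and R already named; no patient, visit or measurement is added. With complete data the four estimated changes equal the mean paired differences, so nothing is given up. The model assumes that data are missing at random given the observed visits. That is weaker than what a completers-only comparison needs, but it is still an assumption: where loss depends on unseen values the bias is reduced and not removed, hence the sensitivity analysis.

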### C (comparison or control)

Our research constitutes a prospective superiority trial, wherein self-control and blind map-reading served as key components. The study was conducted within a single-center and aimed to assess the efficacy of QUS techniques compared to other imaging methods, anthropometric measurements, and laboratory assessments which were designated as control groups.

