### B-mode US

For each participant, B-mode US examination was performed using a US system (RS 85, Samsung Medison, Co. Ltd.) with a convex probe (CA1-7A). All participants were requested to fast for at least 8 h before the US examinations. Hepatic steatosis will be graded subjectively by the operator as no steatosis, mild steatosis, moderate steatosis, severe steatosis. They were be graded based on the following findings: (1) higher echogenicity of the liver, (2) impaired visualization of the intrahepatic vessels, and (3) impaired visualization of the diaphragm and posterior right hepatic lobe due to ultrasound beam attenuation (21).

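### Categorical variables are assigned to the ordinary chi-squared test, although the B-mode grade and any cut-off results are paired within patients

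*Protocol article*

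**What the plan says.** In the protocol article, the Data analysis section fixes two tests in consecutive sentences. For continuous measures: "To compare quantitative data, a paired t-test will be employed". For the rest: "Meanwhile, categorical variables will be analyzed using the chi-squared test". The level is common to both: "The significance level has been predetermined to be 0.05 for all two-sided tests".

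The design is set out under C (comparison or control): "Our research constitutes a prospective superiority trial, wherein self-control and blind map-reading served as key components". There is no parallel arm. Under I (intervention), every patient has every method "before and 1, 3, 6, 12 months after bariatric surgery".

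The categorical outcome that the article describes is in the B-mode US section: "Hepatic steatosis will be graded subjectively by the operator as no steatosis, mild steatosis, moderate steatosis, severe steatosis". B-mode is one of the other imaging methods in the primary endpoint, and its change after surgery falls under the tertiary endpoint. The Data analysis section also sets MRI-PDFF thresholds of 5% and 10%, with Youden cut-offs for QUS and the other methods. These can yield binary results for each patient.

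The Sample size section derives a minimum of 75 patients, raised to 100, from a paired non-parametric test.

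**The concern.** Pearson's chi-squared test for comparing proportions assumes that the groups consist of different people. Here the before and after grades come from the same liver, and so do the results of any two methods. The article makes the pairing explicit for quantitative data and drops it in the next sentence for categorical data.

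The sentence can be carried out in two ways, and neither answers the question:

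- **Stacked table.** Visits or methods are treated as independent groups. The test then uses the wrong variance for the difference. If the paired results agree more often than chance, the variance is overstated and real changes are missed.
- **Patient-level cross-table.** Before is tabulated against after, or method against method. The test then asks whether the two results are associated. A small P value would show that they are related, not that they differ, and could be misreported as a change.

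In addition, the ordinary test ignores the order of the four grades, and it has no counterpart in the paired test used to size the study.

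**Working it through.** **1. The plan's own figure.** The Sample size section gives prevalence 80%, sensitivity 80% and specificity 90%, but no power, comparator rate or effect size. Its inputs therefore do not determine 75. One paired reading takes QUS against the reference:

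- false negatives 0.80 × 0.20 = 0.16; false positives 0.20 × 0.10 = 0.02
- discordant total 0.18; difference 0.14
- McNemar: n = (z_α√0.18 + z_β√(0.18 − 0.14²))² / 0.14²

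Two-sided 0.05 gives n = 70 at 80% power and 93 at 90%. One-sided 0.05 with 90% power gives 75, but neither of those settings is stated. So 75 cannot be confirmed. What matters here is only that the sizing test was a paired one.

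**2. Size of the stacked-table test.** Take a binary outcome with the same proportion p on both occasions and within-patient correlation φ.

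- Variance the test assumes for the difference: 2p(1 − p)/n
- True variance: 2p(1 − p)(1 − φ)/n
- Actual two-sided size at nominal 0.05: 2[1 − Φ(1.96/√(1 − φ))]

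Example with p = 0.80, n = 100, φ = 0.5: assumed SE = √(2 × 0.16/100) = 0.057; true SE = √(0.0032 × 0.5) = 0.040. The effective critical value is 1.96/√0.5 = 2.77.

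| φ (assumed) | Size by formula | Size by simulation, p = 0.80, n = 100 |
|---|---|---|
| −0.2 | 7.4% | 7.5% |
| 0 | 5.0% | 5.2% |
| 0.2 | 2.8% | 3.0% |
| 0.3 | 1.9% | 2.0% |
| 0.5 | 0.6% | 0.6% |

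The simulations used 200,000 trials per setting. McNemar's test stayed at 4.9% to 5.4% in the same five settings.

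**3. Power.** For an assumed change from 0.80 to 0.65 with n = 100, by simulation:

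| φ (assumed) | Chi-squared | McNemar |
|---|---|---|
| 0 | 67% | 66% |
| 0.3 | 70% | 82% |
| 0.5 | 73% | 94% |

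**4. The cross-table reading.** The chi-squared statistic on the patient-level 2 × 2 table is about nφ². With n = 100 this is 100 × 0.09 = 9 at φ = 0.3 and 100 × 0.25 = 25 at φ = 0.5, against a critical value of 3.84. In simulation with equal margins of 0.80, so with no difference at all, the test rejected in 81% and 99% of trials.

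**5. What these figures do not cover.** They apply to a binary outcome, such as a two-way collapse of the grade or a cut-off result. The four-level grade itself was not simulated. The documents give no correlation between visits or between QUS and a comparator. The Sample size inputs imply φ = (0.64 − 0.80 × 0.66)/√(0.80 × 0.20 × 0.66 × 0.34) = 0.59, but that is QUS against MRI-PDFF over all patients. It does not supply the missing values, so 0.3 to 0.5 remains an assumption.

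**The case against.** The strongest reply is that a paired test may have been meant. McNemar's statistic is referred to a chi-squared distribution, the article recognises pairing for the t-test and in the sample size, and an unseen analysis plan may be more precise. This is possible, but it does not rescue the text. The article does not leave the test open: it names one, and it writes the word paired for the t-test and not here. If McNemar's test was intended, saying so is the correction.

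The second reply concerns scope, and it stands. AC-TAI, SC-TSI, CAP, MRI-PDFF, the anthropometric measures and the laboratory values are all continuous. The secondary endpoint, change in QUS parameters, goes to the paired t-test. The evaluation of methods is assigned to correlation, univariable regression on MRI-PDFF and ROC curves.

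Three stronger readings are therefore tempting but unsupported:

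- A reader might infer that the superiority claim rests on chi-squared comparisons of sensitivity and specificity. The article never assigns that comparison to the test. For this trial, sensitivity and specificity appear only as sample-size inputs.
- A reader might infer that every categorical comparison is paired. The article does not list the variables covered, and a split such as MRI-PDFF at or above 10% against below would be between patients.
- A reader might infer a raised risk of false claims. On the stacked-table reading with positive correlation, the error is conservative. Inflation needs negative correlation, which is not expected when the same liver is measured. The cross-table reading can mislead, but through misinterpretation of what is tested.

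**Conclusion.** The sentence is wrong as written for the within-patient comparisons of B-mode grade, and for any before/after or between-method comparison of results dichotomised at the MRI-PDFF or Youden cut-offs. For binary data, with assumed correlations of 0.3 to 0.5, the actual type I error is about 2% to 0.6% instead of 5%. Power falls by about 12 to 21 percentage points in the assumed 0.80 to 0.65 example with 100 patients. At zero correlation the two tests agree. The direction of the effect depends on positive correlation, which is to be expected here but is not given in the documents.

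The weight is moderate. The point should be corrected, but the correlation, regression and ROC analyses and the continuous QUS endpoints stand as they are. It does not by itself undermine the primary endpoint.

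**What to change.** Replace the chi-squared sentence in Data analysis with a paired specification:

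- For binary before/after or between-method comparisons: McNemar's test, with a confidence interval for the paired difference in proportions.
- For B-mode grade: a paired ordinal method, for example the Wilcoxon signed-rank test for two visits, or an ordinal model clustered on patient across the five visits.
- If any categorical comparison between different patients is planned, name it and keep the chi-squared test for that one only.

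This changes analysis wording only. It needs no new data, patients or visits, and it brings the categorical analysis into line with the paired t-test and the paired basis of the sample size.

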## Results

Prior to the fomal study, we recruited 21 Chinese participants who satisfied: (1) age between 18 and 85 years old; (2) with suspected NAFLD, and (3) agreed to receive QUS, and MRI examination. They received ultrasonic examination (TAI, TSI, CAP) and MRI-PDFF (Figure 3).

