**Figure 3 F3:**
[figure not shown]
Quantitative analysis of liver fat in an obese Chinese male. Based on B-mode ultrasound image, the color-coded maps of TAI map (**A**) reflecting center frequency and TSI map (**B**) reflecting Nakagamia parameters are generated. (**C**) MRI-PDFF values were 14.72%.

The average BMI of all participants was 26.43, which meets the diagnostic criteria for overweight. More than 50% of patients (15/21, 71.43%) presented with symptom of right upper abdominal distension. For the value of MRI-PDFF, the average was 13.86%. MRI results from eight patients were below 10%. For MRI-PDFF ≥10%, a total of 13 patients were in this category (13, 62.9%).

All the data were analyzed in R (v4.3.1; R Core Team). A two-sided *P* < 0.05 was considered statistically significant. AC-TAI showed moderate correlations with MRI-PDFF (adjusted *r* = 0.632; *P* < 0.05). Linear correlation between SC-TSI and MRI-PDFF was not significant (*P* = 0.982) (Table 1). For MRI-PDFF ≥10%, SC-TSI showed moderate correlations with MRI-PDFF (adjusted *r* = 0.677; *P* < 0.05) (Figure 4). In a way, the results signified the feasibility of using QUS techniques for postoperative evaluation of bariatric surgery.

**Table 1 T1:** Linear regression between AC-TAI/SC-TSI and other parameters.

Parameters	AC-TAI		SC-TSI	
	Adjusted R	*P*-value	Adjusted R	*P*-value
CAP	0.578	<0.05	0.343	0.070
MRI-PDFF	0.632	<0.05	0.229	0.982

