## Discussion

The rising prevalence of obesity has emerged as a significant public health challenge across the world, affecting both developed and developing nations. Among the numerous adverse consequences of obesity, an important correlation has been established between its degree and the incidence and severity of MAFLD. In fact, obesity has been found to increase the likelihood of developing MAFLD by 4.6 times (22). The natural course of MAFLD indicates that fibrosis manifests in around 32–37% of patients within 3–6 years, and approximately 12% of patients tend to progress to cirrhosis over 8–10 years (23).

Therapeutic interventions such as bariatric surgery have demonstrated potential in ameliorating steatosis, hepatic fibrosis, and necroinflammatory activity, especially for those with morbid obesity and NASH. Weiner et al. (24) conducted a study to evaluate the impact of bariatric surgery on the histological development of NASH. They discovered, through liver biopsy results, that 82.8% of patients exhibited complete regression of MAFLD. Dixon et al. (25) investigated the outcomes of weight loss following Roux-en-Y gastric bypass (RYGB) on liver histology and plasma aminotransferase levels (AST, ALT, and GGT) in 60 severely obese individuals. Results indicated that the mean weight loss was 31.5 ± 18 kg, and there was notable improvement in AST, ALT, GGT, lobular steatosis, inflammation, and fibrosis. Furuya et al. (26) enrolled a cohort of MAFLD patients undergoing RNYGB, and procured a wedge liver biopsy during the operation. The initial evaluation revealed that 67% of the patients had NASH, while 33% had steatosis, and cirrhosis was present in 5.5% of those with NASH. Following an average excess weight loss of 60%, steatosis and fibrosis disappeared in 84% and 75% of the patients respectively.

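### The pilot hints that SC-TSI may not rise or fall steadily with MRI-PDFF around 10%, yet the plan fixes only straight-line, paired-mean and single cut-off analyses and does not ask which way SC-TSI moves.

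*Protocol article*

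**What the plan says.** The Data analysis section of the protocol article names the methods for the QUS parameters. Association is covered by Pearson correlation and by this: "Univariable linear regressions of QUS and other methods on MRI-PDFF were conducted to calculate the adjusted linear correlation coefficient (r"). Quantitative comparisons use a paired t-test, two-sided at 0.05. ROC curves are planned for MRI-PDFF of at least 5% and at least 10%, each with the cut-off that maximises the Youden index.

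The Secondary endpoint section makes the reading of the data depend on whether QUS parameters differ significantly before and after surgery, and treats such a difference as further evidence of feasibility. No direction is required. It adds that "the trend in the changes of hepatic steatosis would evaluate the influence of bariatric surgery on obese individuals".

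The Results section reports a pilot in 21 people with suspected NAFLD. For the whole sample: "Linear correlation between SC-TSI and MRI-PDFF was not significant", with P = 0.982 and an adjusted R of 0.229 in Table 1. For the 13 people in the upper range: "For MRI-PDFF ≥10%, SC-TSI showed moderate correlations with MRI-PDFF", with adjusted r = 0.677 and P < 0.05. No SC-TSI correlation is given for the eight people below 10%. The section concludes that the pilot supports feasibility.

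**The concern.** A clear correlation in 13 of 21 people and none in all 21 do not fit one straight line well. If SC-TSI moves one way with fat above 10% and is displaced the other way below it, a single line averages two different relations. One cut-off then cannot separate the groups, and a mean pre/post difference can cancel or point the wrong way.

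This matters because the trial follows patients whose liver fat is expected to fall. The Discussion cites a bypass cohort in which "steatosis and fibrosis disappeared in 84% and 75% of the patients respectively". If many patients cross the range where the relation changes, a significant SC-TSI change in the wrong direction would still meet the condition in the Secondary endpoint section, and a real fall in fat could appear as no change.

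**Working it through.** **Inputs from the Results section.** n = 21; 13 with MRI-PDFF of at least 10% and 8 below; mean MRI-PDFF 13.86%; SC-TSI against MRI-PDFF: 0.229 with P = 0.982 (all), 0.677 with P < 0.05 (upper 13).

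**1. Reproducing Table 1.** With r = t/√(t² + n − 2) and adjusted R² = 1 − (1 − r²)(n − 1)/(n − 2):
- P = 0.982 on 19 df gives t = 0.0229 and |r| = 0.0229/√(0.0005 + 19) = 0.005.
- Adjusted R² = 1 − (1 − 0.00003)(20/19) = −0.0526. The root of 0.0526 is 0.229, as printed.
- Check on the CAP row: P = 0.070 gives 0.344 (printed 0.343).

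So 0.229 is not a weak positive correlation. It is the root of a negative adjusted R² with the sign dropped.

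**2. The upper subgroup.** 0.677² = 0.4583. R² = 1 − (1 − 0.4583)(11/12) = 0.5035, so |r| = 0.71, t = 3.34 on 11 df, P = 0.007. A figure obtained this way carries no sign.

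**3. Splitting the cross-product.** Total = within upper + within lower + (8 × 13/21) × (difference in mean PDFF) × (difference in mean SC-TSI). The total is about zero and the first term is not, so the other two together must have the opposite sign, whichever sign r has.

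Central case. Assumed, because the article does not give them: lower-group mean PDFF 7%, PDFF SD 5.5 in the upper and 2 in the lower group, equal SC-TSI SD in both (set to 1), no correlation in the lower group.
- Upper mean PDFF = (21 × 13.86 − 8 × 7)/13 = 18.08; difference 11.08.
- Within upper = 12 × 0.71 × 5.5 = 46.9.
- Between-group multiplier = 4.952 × 11.08 = 54.9.
- Difference in mean SC-TSI = −46.9/54.9 = −0.85 SD (−0.82 if 0.68 is used for r).

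Continuing the upper slope would give +0.71/5.5 × 11.08 = +1.43 SD. With lower-group mean 5–8%, upper SD 4–7, r = 0.68–0.71 and lower-group correlation anywhere from −1 to +1, the difference runs from −0.26 to −1.57 SD. Equal group means would need a lower-group correlation of −46.9/(7 × 2) = −3.3, which is impossible when the SC-TSI spreads are equal.

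**4. Precision.** Fisher 95% intervals: overall r −0.43 to 0.44; upper subgroup 0.26 to 0.91. The SE of the mean difference is √(1/8 + 1/13) = 0.45 SD, so 0.85 ± 0.88 just reaches zero. In simulation (evenly spaced PDFF, normal errors, true upper-range correlation 0.26 to 0.71), the joint pilot result had probability below 0.001 under one straight line or a plateau below 10%, and up to 0.17 under a reversal. That reversal had a slope below 10% chosen to match the pilot (3.5 times as steep), which favours it. Taken singly, a true upper-range r of 0.26 with a plateau gives an overall r of −0.15 to 0.64, which includes the observed value.

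**5. Effect on the planned paired t-test.** n = 75 (the plan's stated minimum). Assumed: PDFF SD 5 before and 2.5 after surgery, upper slope positive with r = 0.71 and SD 6, slope below 10% a multiple of the slope above. Each cell is the chance of a significant fall / rise in SC-TSI.

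| Mean PDFF before → after | Plateau below 10% | Slope ratio −2 | Slope ratio −3.3 |
|---|---|---|---|
| 18.7 → 10 | 100% / 0% | 100% / 0% | 97% / 0% |
| 18.7 → 8 | 100% / 0% | 92% / 0% | 14% / 0% |
| 18.7 → 5 | 100% / 0% | 0% / 13% | 0% / 100% |
| 14 → 5 | 99% / 0% | 0% / 93% | 0% / 100% |

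PDFF falls in every row. Whether SC-TSI follows depends on the shape below 10% and on how far PDFF falls, and the documents give neither.

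**The case against.** The strongest counter-evidence is in the article. The Discussion cites a study in MAFLD patients against MRI-PDFF with SC-TSI r = 0.727 and an area under the ROC curve of 0.964 for fat of at least 5%, both better than AC-TAI. An area that high at 5% is hard to reconcile with low-fat livers reading as fatty. This stands, and it means the two sources conflict.

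A reader might infer from the pilot that SC-TSI does reverse across the range through which surgery takes patients, so that the secondary endpoint will mislead. The documents do not support that. The pilot is a cross-section of 21 people with mean BMI 26.43, below the trial's entry limit of 27.5, and none is described as a surgical patient. Within-person change does not follow from it. The 10% split looks post hoc. Unequal SC-TSI spread or a few outliers could contribute. No MRI-PDFF values before or after bypass are given; the 84% is disappearance of steatosis in a cited cohort, not a PDFF trajectory. The scatterplot that might settle the shape is not available here.

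Part of the protection already exists. MRI-PDFF is measured at every visit, imaging changes are examined under the tertiary endpoint, AC-TAI and SC-TSI are calculated and tabulated separately, and ROC curves are planned at two thresholds. A conflict with MRI-PDFF would therefore be visible to someone looking for it.

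Spline detail is often left to an analysis plan. What remains is that the article commits to linear methods, and to a reading rule without direction, that its own pilot calls into question.

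**Conclusion.** The point holds as a signal that the plan should be able to test. In the pilot sample, r of about 0 overall and |r| of about 0.71 above 10% require an offsetting contribution from the eight people below 10%; this follows from the printed figures. Its size, 0.26 to 1.57 SD with about 0.85 central, rests on assumed PDFF means and SDs and on equal SC-TSI spread. Its extension to bypass patients is uncertain, and the cited study points the other way. If the relation is monotone, or PDFF ends near 10%, the planned paired comparison works. If the reversal is real and PDFF falls well below 10%, that comparison can miss the fall or show a significant change the wrong way, and the Secondary endpoint section would still count the latter as support.

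**What to change.** In the Data analysis section, pre-specify a test of linearity for SC-TSI on same-day MRI-PDFF over all visits, using a restricted cubic spline or a segment at 10% and allowing for repeated measures within patient. Report the association separately for MRI-PDFF below 10% and at or above 10%.

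In the Secondary endpoint section, state that an SC-TSI change is read as a change in steatosis only if it agrees in direction with the MRI-PDFF change and the fitted curve is monotone over the observed PDFF range. Name MRI-PDFF as the reference for the post-surgical steatosis trend.

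In the Results section, give the sign of the subgroup correlation, add the result for the eight people below 10%, and correct the 0.229 entry.

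No new data are needed. The cost is a somewhat more complex report and possibly a narrower claim for SC-TSI.
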